**Methods and analysis:**

This secondary data analysis protocol aims to evaluate different HIVST distribution models from a prospective study implemented during November 2017 and December 2020 by Ezintsha, a subdivision of Wits Reproductive Health and HIV Institute. Routinely collected distribution and self-reported HIVST outcomes data will be deidentified and analysed. The main outcomes of interest are linkage to care and treatment among HIVST users who report a reactive HIVST result. Additionally, we plan to determine sociodemographic factors associated with linkage to care and treatment among HIVST users. Descriptive statistics will be used to describe the variables of interest, and modified Poisson regression with robust variance estimation will be performed to identify factors associated with linkage to care and treatment among HIVST users who report a reactive HIVST result. Risk ratios and 95% CIs for the risk ratios will be reported.

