
Wits RHI was one of the implementing partner of the STAR Initiative in South Africa and implemented the project in Gauteng, North West, Mpumalanga and Limpopo provinces of South Africa. Approximately 1.2 million HIVST kits were distributed, primarily targeting testing men, young people and key populations. Under the Wits RHI implemented programme, HIVST was offered if recipients did not know their current HIV status or received an HIV-negative result in the last HIV test taken >3 months ago. HIVST was not offered if the recipient was below the age of 12 or known HIV positive or if there was an identified risk of social harm, such as suicidal thoughts, gender-based violence or coerced testing.

This secondary data analysis protocol aims to evaluate different HIVST distribution models from a prospective HIVST study implemented in South Africa. The main outcomes of interest are linkage to care and treatment among HIVST users who reported a reactive HIVST result by examining the proportion of HIVST recipients who reported a reactive HIVST result and sought HIV confirmatory testing and entry into care among clients who received HIVST kits via the different distribution approaches implemented under the STAR Initiative in South Africa.

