	Workplace	This involved distribution of HIVST in formal workplaces with a focus on mining, manufacturing, construction, petroleum, agriculture and security sectors. Employees were offered an HIVST test kit to take home. All female employees were offered an HIVST kit for their male partners. 5% of the sample of primary consenting recipients of HIVST was telephonically followed up to obtain information on HIVST usage, result, linkage to care and ART initiation. Beginning August 2019, clients were also offered mHealth platforms to self-report on use, result and linkage to care.
Secondary-based distribution	Antenatal	After a demonstration and social harm assessment, all first visit antenatal attendees were offered HIVST to take home to support testing their sexual partners. The HIVST modality was not intended to replace facility based RDT testing but support testing of male partners. Women could take HIVST kit for herself to support home disclosure. Consenting women were followed up by telephone or at next visit to acquire information on whether HIVST had been used by partner(s) and for test result and linkage data.
	Index testing	HIVST is offered to newly diagnosed HIV-positive clients (ART clinic) to facilitate partner notification. Telephonic follow-up of HIV-positive index to ascertain index partner uptake of HIVST, linkage of positive sexual partner to confirmative testing and treatment initiation.

GP, general practitioner; HIVSS, HIV self-screening; HTS, HIV testing service; mHealth, mobile health; RDT, rapid diagnostic testing; Wits RHI, Wits Reproductive Health and HIV Institute.

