### Data collection

During HIVST distribution, recipients’ age, gender, HIV testing frequency, as well as partner demographics were collected. Recipients were issued a barcode sticker that accompanies the HIVST kits. Duplicate barcodes were attached to the partner’s HIVST kit(s) when provided. This barcode number was entered onto the participant’s distribution data collection form and was used as the unique identifier for recipients and their associated HIVST kits issued. At distribution, HIVST recipients were also informed of the available options for support with testing, linkage to care as well as self-reported follow-up. Consent was sought from recipients for follow-up through one of the four self-reporting platforms offered on the project: telephonic, interactive voice response (IVR), Progressive WebApp (PWA) or WhatsApp messaging (business version). The different self-reporting platforms were offered to provide participants the ability to choose the option that may work best for them and inform which options will be included in the national HIVST policy to support the scale-up of HIVST and to help collect HIVST use and results data nationally. A standardised follow-up questionnaire was administered to consenting HIV self-testers and collected responses on the following: did you use the test? what was the HIV self-test result? did you request confirmatory testing? did you get confirmatory testing? were you linked to care? were you initiated on antiretorvial therapy (ART)? This set of questions was standard across the four follow-up platforms.

For HIVST recipients preferring follow-up by telephone, up to three telephone calls were conducted by a trained linkage officer at 2, 4 and 6 weeks post-distribution to obtain responses on the aforementioned described set of questions. IVR is an automated telephone system that interacts through short messages and calls with HIVST recipients to confidentially self-report their results. The first automated reminder SMS message to use and self-report HIVST results was sent within 24 hours following distribution. A second short message was sent on day 3 (SMS 2). If reporting had not been done at these two interactions, the IVR system automatically called the participant on day 7 to self-report results. Recipients also had the option to make an inbound call to the platform for support and self-reporting at any time postdistribution.

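### The reactive-result denominator can include people diagnosed or in care before the kit, mainly through secondary distribution, and the listed data items cannot separate them from new linkage

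*Protocol article*

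**What the plan says.** The Abstract of the protocol article defines the outcome population: "The main outcomes of interest are linkage to care and treatment among HIVST users who report a reactive HIVST result". The Introduction repeats this. Neither place limits it to people not previously diagnosed.

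The section on the STAR Initiative in South Africa gives the eligibility rule: "HIVST was offered if recipients did not know their current HIV status or received an HIV-negative result in the last HIV test taken >3 months" earlier, and "HIVST was not offered if the recipient was below the age of 12 or known HIV positive".

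Three parts of Table 1 (Study design) do not fit neatly under that rule:

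- **Antenatal row.** The offer is general: "all first visit antenatal attendees were offered HIVST to take home to support testing their sexual partners". Routine facility testing continues: "The HIVST modality was not intended to replace facility based RDT testing but support testing of male partners". The woman may also have a kit of her own: "Women could take HIVST kit for herself to support home disclosure".
- **Index testing row.** "HIVST is offered to newly diagnosed HIV-positive clients (ART clinic) to facilitate partner notification". Follow-up in this row concerns the partner.
- **Kits passed on.** Sex workers may take up to five kits for their networks. Kits for partners are also described for hotspots, transport hubs, door-to-door, GP and nurse-led clinics, pharmacies and workplaces.

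The Data collection section lists age, gender, testing frequency and partner demographics at distribution, followed by a standard set of follow-up questions that ends with "were you linked to care? were you initiated on antiretorvial therapy (ART". None of the listed items asks about diagnosis or ART before the kit. Partner kits carry a duplicate of the recipient's barcode.

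**The concern.** A reader will take linkage among reactive users to mean people newly found by self-testing who then entered care. The eligibility rule supports that reading for someone handed a kit for personal use. It gives no such assurance for someone who receives the kit from a partner, a sex worker or a relative, because no status check on that person is described. It is also uncertain for an antenatal woman who is still tested at the facility and uses a kit at home for disclosure: her status may already be known to her.

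A previously diagnosed user who reports a reactive result can answer the linkage and ART questions either way. Someone already treated may say yes because they are on ART, or no because the kit did not lead to a new start. The planned analysis then combines two different quantities.

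This bears on three planned outputs under Statistical analysis: the pooled proportions, the binomial test against a published proportion, and the comparisons by modality. The share of secondary users differs between modalities by design, so any mixing would be uneven. The multiple imputation plan does not help, since it fills missing values and does not separate two meanings of one recorded answer.

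**Working it through.** The article gives no expected linkage proportion, no sample size and no share of previously diagnosed users, so there is no stated figure to reproduce. The check has two parts.

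**1. Who is covered by the status screen**

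| Group | Status screen described? | Can enter the reactive denominator? |
|---|---|---|
| Primary recipient using the kit | Yes, the STAR section rule | Yes |
| Antenatal woman using her own kit | Unclear: general offer, facility testing retained | Unclear: follow-up centres on partner use, and it is not said whose result and linkage are recorded |
| Index client | Known positive, so at odds with the rule | Not described as a tester; the outcome is the partner's |
| Partner or network member | None described | Yes |

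The integrated mobile and outpatient rows describe only onsite testing and no kits for partners. The antenatal, index and sex-worker rows are mainly or wholly secondary. The remaining rows mix primary kits with partner kits.

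**2. What mixing would do (illustration; every value assumed)**

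Let *f* be the share of reactive reporters already diagnosed or in care, *p* the linkage among the newly identified, and *q* the share of the already diagnosed who are recorded as linked.

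Observed linkage = (1 − f)p + fq, so the bias is f(q − p). It is positive if q > p, negative if q < p, and zero if q = p.

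| p | f | q = 1 | q = 0 |
|---|---|---|---|
| 50% | 5% | 52.5% | 47.5% |
| 50% | 10% | 55% | 45% |
| 50% | 20% | 60% | 40% |
| 50% | 30% | 65% | 35% |
| 30% | 20% | 44% | 24% |
| 70% | 20% | 76% | 56% |

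For example, with p = 50% and f = 10%: 0.90 × 0.50 + 0.10 × 1 = 0.55, or 0.90 × 0.50 + 0 = 0.45.

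*Modality contrast.* Suppose two modalities both have 50% new linkage, one with f = 0 and the other with f = 20%. The risk ratio is 0.60/0.50 = 1.20 if q = 1 and 0.40/0.50 = 0.80 if q = 0, although new linkage is identical.

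*Benchmark test.* Take new linkage equal to the benchmark p0 = 50%, with q = 1 and a two-sided 0.05 level. With p1 = (1 − f)p0 + f, SE0 = √[p0(1 − p0)/n], SE1 = √[p1(1 − p1)/n] and c = 1.96 × SE0, the normal approximation gives

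P(reject) = 1 − Φ[(p0 + c − p1)/SE1] + Φ[(p0 − c − p1)/SE1].

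| n reactive | f = 5% | f = 10% | f = 20% |
|---|---|---|---|
| 200 | 11% | 29% | 81% |
| 500 | 20% | 61% | 99.5% |
| 1000 | 35% | 89% | about 100% |

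For n = 500 and f = 10%: SE0 = 0.0224, c = 0.0438, SE1 = 0.0222, so P(reject) = 0.61. A larger sample makes the test more sensitive to mixing; it does not dilute it.

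The scenarios q = 1 and q = 0 are extremes. Here f is the share among all users analysed, so for the pooled estimate it would be small if secondary users are few.

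**The case against.** The strongest reply is that the article shows only a possibility. Several stronger readings are tempting, and the text does not support them.

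- *The denominator does contain people already in care.* Nothing says so. The antenatal sentence does not say that the woman is HIV positive or in care. A woman disclosing a negative result would normally self-test non-reactive and never enter the denominator.
- *Index clients' own results are counted.* The kit is for the partner, and follow-up concerns the partner's uptake and linkage. The index client matters only for the mismatch with the eligibility rule, not as a counted outcome.
- *The plan claims linkage caused by self-testing.* It states proportions and associated factors. A single-group proportion would not be causal even with a clean denominator. The Discussion's promise to identify the best channels is a separate matter, and the Limitations section plays down comparison between modalities.
- *Linkage is overstated.* The direction depends on q relative to p, and neither is known.

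The lack of a screen for second-hand users is also read from silence, and how linkage is coded may be set out in a full protocol or analysis plan that is not shown. Finally, making primary recipients the main analysis would remove most of the secondary models from a study meant to evaluate all of them.

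These limits are accepted. What stands is that the rule and Table 1 do not agree as written, that the reactive denominator carries no prior-status restriction, and that the listed data items offer no way to apply one directly. Distribution ended in December 2020, so an unseen analysis plan could restrict or stratify but could hardly add a baseline question.

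**Conclusion.** The point holds as a limited one. The denominator can include people diagnosed or in care before the kit, and reported linkage may then mix new entry to care with existing care, unevenly by modality. The extent and direction are unknown. Under assumed values, a 10% share moves a 50% proportion by 5 percentage points either way, and a 20% share by 10 points. Differences of that size could decide the benchmark test or a modality contrast, but whether they occur depends on a share that the documents do not give. This is a worthwhile and inexpensive improvement to the analysis, not a reason to distrust the data set as a whole.

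**What to change.** - Keep the planned all-user analysis, and define linkage as new entry to care after the kit.
- Report linkage and ART separately for primary recipients and for secondary distribution (antenatal, index, sex-worker networks, and partner kits where they can be identified). Label the secondary results *linkage or already in care*.
- Repeat the pooled proportion and the benchmark test as a sensitivity analysis restricted to primary recipients.
- State whether antenatal women's own kits count, and exclude them from the denominator where their use is recorded.
- Reconcile the eligibility statement in the STAR section with the antenatal and index rows of Table 1. Which rule was applied is for the investigators to state.

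The cost is some added text in the analysis plan and one more stratification. The restricted estimate will rest on fewer reactive users and be less precise. Modality is already recorded, but it does not isolate partner kits within hotspot, transport hub, door-to-door, GP and nurse-led clinic, pharmacy and workplace distribution. Because those kits carry duplicate barcodes, the separation may be incomplete, and the report should say so.

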### Data collection

During HIVST distribution, recipients’ age, gender, HIV testing frequency, as well as partner demographics were collected. Recipients were issued a barcode sticker that accompanies the HIVST kits. Duplicate barcodes were attached to the partner’s HIVST kit(s) when provided. This barcode number was entered onto the participant’s distribution data collection form and was used as the unique identifier for recipients and their associated HIVST kits issued. At distribution, HIVST recipients were also informed of the available options for support with testing, linkage to care as well as self-reported follow-up. Consent was sought from recipients for follow-up through one of the four self-reporting platforms offered on the project: telephonic, interactive voice response (IVR), Progressive WebApp (PWA) or WhatsApp messaging (business version). The different self-reporting platforms were offered to provide participants the ability to choose the option that may work best for them and inform which options will be included in the national HIVST policy to support the scale-up of HIVST and to help collect HIVST use and results data nationally. A standardised follow-up questionnaire was administered to consenting HIV self-testers and collected responses on the following: did you use the test? what was the HIV self-test result? did you request confirmatory testing? did you get confirmatory testing? were you linked to care? were you initiated on antiretorvial therapy (ART)? This set of questions was standard across the four follow-up platforms.

For HIVST recipients preferring follow-up by telephone, up to three telephone calls were conducted by a trained linkage officer at 2, 4 and 6 weeks post-distribution to obtain responses on the aforementioned described set of questions. IVR is an automated telephone system that interacts through short messages and calls with HIVST recipients to confidentially self-report their results. The first automated reminder SMS message to use and self-report HIVST results was sent within 24 hours following distribution. A second short message was sent on day 3 (SMS 2). If reporting had not been done at these two interactions, the IVR system automatically called the participant on day 7 to self-report results. Recipients also had the option to make an inbound call to the platform for support and self-reporting at any time postdistribution.

PWA is a mobile phone-based tool to support participants through self-testing and eventual confirmatory testing. It is accessible as a mobile site but is also downloadable to a phone, where the full site contents can be cached for offline browsing. Users that selected the web app received an SMS 24 hours following distribution, which provided them with a free URL link to access the PWA for registration on the application. Once subscribed, participants were able to access the website link and to self-report their results.

The Chatbot on a WhatsApp for business platform allowed users to send text and voice messages, make voice and video calls, and share images, documents, user locations and other media. HIVST recipients who selected follow-up and linkage support via the WhatsApp platform received a WhatsApp message 24 hours following distribution to confirm subscription. Once subscribed, participants were able to access the platform, which included terms and conditions, assistance through self-testing process and ultimately self-reporting of their results.

We will merge routinely collected programme distribution and HIVST users’ self-reported data. The survey responses were captured and linked to HIVST recipients’ distribution data via telephone number and barcode onto the project database. Data captured into project database were access controlled and regularly checked for quality, including data reconciliations and a data verification.

### Statistical analysis

Data for the secondary analysis will be deidentified and the analysis will be conducted between April and July 2021. Continuous variables will be expressed as means (±SD) or median and IQR as appropriate. Frequencies and proportions will be used to describe categorical variables. Binomial test will be used to determine whether the proportion of linkage to care and receipt of treatment among HIVST users equal to a prespecified proportion based on a recently published South Africa HIVST study.^17^ Differences in the proportions of linkage to care and receipt of treatment among HIVST users by distribution modality and other sociodemographic characteristics will be assessed using χ^2^ test or Fisher’s exact test, as appropriate. Unadjusted and multivariable adjusted relative risks of linkage to care and receipt of treatment among HIVST will be calculated using modified Poisson regression with robust variance estimation. Risk ratios and 95% CIs for the risk ratios will be reported. A two-tailed p value of <0.05 will be considered statistically significant. All analyses will be performed using STATA and SAS V.9.4.

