	Door-to-door	Within a specific mapped community or geographical location, peer educators and/or trained counsellors move from one household to another and offer HIVST to eligible clients residing there. Clients were offered HIVST with the option of either being directly assisted (in the presence of a healthcare provider) or unassisted. Clients who self-report reactive results were offered the option to confirm their results onsite. All women and men who had male partners were offered oral HIVST tests for their partners. To collect information on outcomes of HIVST use, result, linkage to care and uptake of ART, peer educators went back to the residences of all consenting clients.
	Integrated HTS (mobile)	This modality involved the integration of HIVST into existing mobile HIV testing activities. Clients were offered a choice between HIVST onsite or RDT with a counsellor. HIVST kits were distributed to individual clients after a demonstration of how to use them. Clients who opted for HIVST were only offered onsite testing with the option to confirm a reactive HIVST result immediately. Clients who confirmed reactive were referred to nearby health facilities for ART initiation. To collect information on outcomes of linkage to care and uptake of ART, linkage officers checked ART registers of referral health facilities. Integration of HIVST into mobile HTS did not displace traditional blood-based RDT uptake but provided a screening option of increased yield and efficiency for triaging clients for further managed healthcare.
Key population distribution	Sex worker	This modality was implemented alongside the Wits RHI sex worker programme, which provides various health services to sex workers at static sex worker clinics and at outreach sites. Sex workers were offered up to five HIVST kits to take for their network, which would either be their non-client sexual partners, their clients, other sex workers not accessing HTS or a member of the family or friend considered by the sex worker to be at high risk of HIV. This modality was intended to be a secondary only distribution modality; however, sex workers could use one kit for themselves if they needed to test themselves together with one of their recipients. All consenting sex workers were telephonically followed up to determine the usage, linkage to care and ART initiation status of their networks.

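### Linkage and treatment are compared by modality as if users were independent, although users cluster in distribution sites and, in three modalities, one recipient reports for other testers

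*Protocol article*

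**What the plan says.** **Analysis.** The Statistical analysis section of the protocol article names a binomial test of the linkage and treatment proportions against a prespecified value. It names chi-square or Fisher's exact tests for differences by modality and sociodemographic group, and "modified Poisson regression with robust variance estimation" for unadjusted and adjusted relative risks. Significance is two-sided at 0.05. No cluster unit is named for any of these.

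**How users arise.** Table 1 (Study design) describes distribution through pop-up sites, transport hubs, mapped communities, clinics, pharmacies and workplaces. In the sex worker modality, "Sex workers were offered up to five HIVST kits to take for their network", and the sex workers were "telephonically followed up to determine the usage, linkage to care and ART initiation status of their networks". Antenatal women were contacted to "acquire information on whether HIVST had been used by partner(s) and for test result and linkage data". Index clients were telephoned about their partners in the same way.

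**Identifier and merge.** Under Data collection, "Duplicate barcodes were attached to the partner’s HIVST kit(s) when provided", and the barcode "was used as the unique identifier for recipients and their associated HIVST kits issued". Survey responses were "linked to HIVST recipients’ distribution data via telephone number and barcode onto the project database". The same section says partner demographics were collected. The Handling missing data section lists distribution location among the variables held.

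**The concern.** There are two separate issues.

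**Variance.** The sandwich variance in modified Poisson regression corrects the Poisson variance for a binary outcome. It allows for clustering only when a cluster unit is declared. The binomial, chi-square and Fisher tests make no such allowance. Users of one site share staff, referral routes and onsite services, so their linkage outcomes are likely to be correlated. Because the site largely determines the modality, the modality comparison is the one most exposed. The Discussion says the findings will identify which channels work best and should be adopted nationally, so overstated precision here could reach policy.

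**Whose outcome it is.** When a recipient reports for a partner, both the barcode and the telephone number are the recipient's. Those two keys cannot tell the two people apart. The recipient's age, gender or testing frequency could then be attached to the partner's outcome, and sociodemographic factors are a stated objective of the analysis.

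**Working it through.** The article gives no number of sites, cluster size or intracluster correlation (ICC), so there is no figure to reproduce. Cluster sizes and ICCs below are assumptions. The 0.05 threshold is from the Statistical analysis section. The HIV prevalences of 12.7% and 19.1% are from the Introduction and serve only as a stand-in for the share of kits that are reactive.

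**Formulas.** Design effect: DEFF = 1 + (m − 1) × ICC. True two-sided error of a row-level test of a factor constant within cluster: 2 × [1 − Φ(1.96/√DEFF)]. With DEFF = 1 this returns 5%. Row-level intervals are too narrow by a factor of √DEFF.

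**Site level**, m = reactive users per site:

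| m | ICC | DEFF | √DEFF | True error |
|---|---|---|---|---|
| 10 | 0.05 | 1.45 | 1.20 | 10.4% |
| 10 | 0.10 | 1.90 | 1.38 | 15.5% |
| 20 | 0.05 | 1.95 | 1.40 | 16.0% |
| 20 | 0.10 | 2.90 | 1.70 | 25.0% |

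For the first row: 1 + 9 × 0.05 = 1.45; 1.96/√1.45 = 1.63; two-sided tail 10.4%. With a smaller ICC of 0.02 and m = 20, DEFF is 1.38 and the error 9.5%.

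**Reporter level, reactive users only.** If a recipient takes five kits and reactivity is independent, the size-weighted number of reactive testers per reporter is 1 + 4p, where p is the share reactive.

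- p = 0.127: 1.51 reactive testers. ICC 0.1 gives DEFF 1.05 and error 5.6%.
- p = 0.191: 1.76 reactive testers. ICC 0.5 gives DEFF 1.38 and error 9.6%.
- Recipient plus one partner: m = 1 + p, or 1.13 to 1.19. ICC 0.2 to 0.3 gives an error of about 5.3% to 5.7%.

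**Simulation check.** 600 runs per scenario, beta-binomial clusters of equal size, an outcome probability of 0.6 in both groups, and group fixed by cluster:

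| Clusters per group | m | ICC | Ordinary robust | Chi-square | Cluster-robust |
|---|---|---|---|---|---|
| 30 | 20 | 0.02 | 10.2% | 10.5% | 5.0% |
| 30 | 20 | 0.05 | 17.8% | 17.8% | 6.0% |
| 30 | 50 | 0.05 | 31.5% | 31.5% | 6.3% |
| 200 | 5 | 0.30 | 21.7% | 21.7% | 6.0% |

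Ordinary robust variance performs like the chi-square test, and declaring the cluster brings the error back to about 5–6%. The last row treats all five testers of a reporter as analysed, so it is more severe than the reactive-only set.

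**Linkage.** No arithmetic applies. Set side by side, the barcode covers a recipient and all associated kits, responses are tied to the recipient's record by barcode and telephone number, and in three modalities the respondent speaks for someone else. No rule for separating recipient outcomes from partner outcomes is described.

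**The case against.** The strongest reply is that the regression wording is compatible with a cluster option, and that a condensed article may leave this option to a fuller plan. That stands for the regression: a reader might infer that it will certainly treat rows as independent, but the article only leaves the unit unnamed. The reply does not help the binomial, chi-square and Fisher tests, which the article names outright, or the linkage keys.

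A reader might also infer that age and gender are misclassified wherever kits went to partners. The text does not support that. Telephone follow-up at hotspots, transport hubs and workplaces is of primary recipients. Explicit proxy reporting appears only in the sex worker, antenatal and index modalities, where follow-up is directed at the partner or network. Partner demographics were collected, data reconciliation and verification are described, and nothing says the partner data go unused. Nor does the text show an index client's own treatment status being recorded as a partner's.

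Repeat testing over three years is a weak argument here. The main analysis covers users with a reactive result, and people known to be positive were not offered kits, so repeat reactive rows should be uncommon.

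Finally, the Limitations section says the focus is less on comparing modalities. That lowers the stakes, but the Discussion's claim about which channels work best restores much of them.

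**Conclusion.** The point holds in two parts. First, the named simple tests ignore clustering by site, and the regression names no cluster unit. If outcomes correlate within site, modality intervals are too narrow, by a factor of 1.20 to 1.70 under 10–20 reactive users per site and ICC 0.05–0.10, with a true error of about 10–25% at a nominal 5%. These inputs are assumed, and the figures apply to factors constant within site. They should not be carried over to age and gender, which vary within sites and are less affected. If one facility hosted several modalities, the modality effect would also be smaller. Clustering by reporter is minor among reactive users, at about 5–10%.

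Second, in the three proxy-reporting modalities, the described keys identify the recipient rather than the tester. Misattribution of age and gender is a risk that the described merge leaves open. The article does not show that it occurred, and its extent cannot be sized from the text.

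**What to change.** **Variance.** State that the Poisson models use cluster-robust variance at distribution site, within which recipients and their partners fall, with a small-sample correction. Replace the simple binomial, chi-square and Fisher tests with versions based on the same clustered variance, for example Rao-Scott. Distribution location is already among the variables held, so this needs little more than a software option.

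**Linkage.** At the merge, before deidentification removes the telephone number, create one record per tester: barcode, kit or person index, recipient/partner flag, and self/proxy flag. The index is needed because barcode, role and telephone number together still cannot separate several network members reported by one person. Attach the collected partner demographics to partner outcomes. Where the tester cannot be resolved, leave the report out of the age and gender models only, and add a sensitivity analysis that includes it.

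**Cost.** Intervals widen, the merge takes some work, and some secondary-distribution records leave the covariate models. That loss is selective, hence the sensitivity analysis.
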